4. MATERIALS AND METHODS

4.1. Study design:

This is a randomized, open, parallel-group clinical trial to investigate the safety and efficacy of a new cervical device called DUDA (Uterine Device for Dilatation of the Endocervical Canal). As this is an intervention in which the doctor must know the result of the randomization for implantation of the device, he will not be blind. The study will be carried out sequentially in two stages, the first being intended to exclusively evaluate the safety of using the device and the second to evaluate safety and effectiveness.

4.2. Study Location:

The study will be carried out in the Oncology and Prevention Gynecology Departments of the Barretos Cancer Hospital/Pio XII Foundation (Barretos, SP).

4.3. Inclusion criteria:

For inclusion, all criteria must be present:

a) Histopathological diagnosis of NIC2/3 on cervical biopsy;

b) Indication for performing CAF (high-frequency surgery);

c) Age between 18 and 65 years;

4.4. Exclusion criteria:

For exclusion, any of the following criteria must be present:

a) Pregnant women before CAF;

b) Previous conization / CAF history;

c) Women who do not understand or accept the study;

d) Women subjected to a regime that determines significant vulnerability to the participant (ex: prisoners, indigenous, etc.)

4.5. Description of the Endocervical Canal Dilatation Device (DUDA):

It is a plastic device (polyacetal) designed by the responsible researcher, made by hand on a lathe through the wear of a cylindrical part.

Polyacetal is a plastic material. This material is unique, pure (without additives) with exceptional dimensional stability, low friction coefficient, low moisture absorption and high abrasion resistance. It maintains characteristics when immersed in hot water. High durability, is resistant to biological attacks and impacts, and can even hold weights indefinitely. It also has low weight, high melting point, good impact resistance, high lubricant, thermal insulation, low friction coefficient, high resistance to wear and chemical agents, thus being able to substitute bronze, brass, aluminum with advantages. In addition to the advantages presented, this material is inexpensive. It does not have a porous surface and, therefore, the concentration of substances is inert. As a consequence, it does not generate biofilm, which reduces the risk of infections associated with it. Before use, the device will be sterilized according to the Institution's operational procedure.

Cylindrical at one of its ends, with 4 holes (where the points will be anchored), 2.5 cm in diameter, accompanied by a cylindrical rod with a diameter of 4 mm, central lumen and 2 cm in length (Figures 3, 4 and 5). The nail is introduced into the endocervical canal and the larger cylindrical part is in contact with the external surface of the cervix.

[figure not shown]

Figure 3: Anterior view of the device (DUDA).

[figure not shown]

Figure 4: Rear view of the device (DUDA).

[figure not shown]

Figure 5: Side view of the device (DUDA).

4.6. Description of the conization technique with high-frequency surgery (CAF):

           High-frequency surgery (CAF) is performed by means of a diathermic loop (Figures 1 and 2) connected to an energy source, in order to remove all the so-called transformation zone of the cervix. The size of the resection can be programmed by the surgeon based on the size of the colposcopic lesion and from there choose the best loop size to be used. It is worth remembering that this procedure is part of the conventional treatment of cervical intraepithelial neoplasms and its indication regardless of the acceptance or not of the research participant. Therefore, CAF does not represent the experimental part of the study.

The CAF lasts approximately 20 minutes and follows the technical steps described below:

1) Intravenous sedation;

2) Positioning the patient in the supine position on Allen's leggings and in the lithotomy position;

3) Asepsis with degerming iodine throughout the perineal and vaginal region. If the patient has an allergy to iodine, asepsis is performed with chlorhexidine gluconate solutions;

4) Placement of sterile surgical drapes;

5) Introduction of the vaginal speculum and identification of the cervix;

6) Passage of acetic acid and Lugol´s iodine in the cervix and vaginal walls to identify positive acetowhite and iodine areas;

7) Local anesthesia with 2% lidocaine with a vasoconstrictor, infusing 2 ml in each quadrant of the cervix (3, 6, 9 and 12h);

8) Passage of the diathermic loop connected to the generating source in “cut” mode (level 60) in a single pass, with or without enlarging the endocervical canal (depending on the indication of each case);

9) Hemostasis with a "ball" electrode connected to the generating source in "coagulation" mode (level 60).

After this surgical procedure, the patient remains in the hospital for a few more hours for recovery from anesthesia and observation of eventual postoperative bleeding. The patient is discharged from the hospital with guidance on the use of analgesics (if necessary) and to abstain from sexual intercourse for at least 30 days due to the risk of bleeding during intercourse.

4.7 Procedure for placing the endocervical device (DUDA):

After the end of the CAF, and with the patient still positioned on the operating table, the surgeon will place the DUDA device on the cervix. Device deployment is quick and requires no more than 5 minutes. It should be noted that this procedure represents the experimental part of the study.

The surgeon will carefully insert the nail into the endocervical canal until the flat circular surface of the device rests on the cervix. By means of the simple suture in four points (2-0 polypropylene thread, atraumatic needle), the device will be fixed to the surface of the cervix. In the event that the residual neck has a very flat surface, the device may be attached to the lateral fornices.

4.8 Criteria for not placing or removing the device:

Even if the participant has signed the Free and Informed Consent Form and the randomization has already been carried out, the DUDA device will not be placed on patients who have any complications during the performance of the CAF and that require additional procedures, such as bed bleeding. surgical procedure requiring hemostatic procedures with suture and/or use of a vaginal tampon.

Participants whose anatomopathological report of the conization surgical specimen demonstrates invasive cervical carcinoma will have the device removed before the deadline and will be referred for appropriate cancer treatment.

The early removal of the device may be carried out if, after its placement, the researcher identifies potential risk to the research participant or also at the request of the same.

4.9 Study steps:

This is a study whose main objective is to evaluate the safety and effectiveness of a new therapeutic device. The study design foresees the realization of two distinct sequential steps. The first stage aims to determine the safety of using the DUDA device in initially 25 women. Concluding that the device is safe for the participants, we will proceed to the second stage, in which, in addition to safety, the effectiveness of the device in preventing post-conization endocervical canal stenosis (CAF) will be evaluated in a study randomized, open and parallel study with 240 women (120 in each arm). This study design aims to bring greater security to the research participants, avoiding recruiting a large number of women unnecessarily.

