3. OBJECTIVES

3.1. Primary objective:

To evaluate the effectiveness of a new cervical device called DUDA in preventing late cervical canal stenosis in women undergoing conization with a high-frequency scalpel.

3.2. Secondary objectives:

3.2.1. Assess the safety of using the device;

3.2.2. Compare the quality of life in women with and without the device after surgery;

3.2.3. Compare the rate of visualization of the squamous-columnar junction (JEC) in women who used the device or not (3 and 6 months after surgery);

3.2.4. Describe menstrual periods in women who used device placement after surgery.

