Endocervical canal stenosis (early and late) will be assessed through clinical information and physical examination at each visit to the hospital after surgery. The participant will be asked about menstrual flow and dysmenorrhea during anamnesis, which would indirectly show whether the endocervical canal is patent or not. In the physical examination, after viewing the cervix through specular examination, the doctor will check the permeability of the canal by introducing the hysterometer through the cervical canal. The difficulty of introducing the 2.5mm hysterometer through the channel will be noted according to the following scale:

The possible passage of the hysterometer?

( ) No difficulty

( ) Little / Moderate difficulty, however possible passage of the hysterometer

( ) Could not pass

4.10.3. Quality of life:

Quality of life questionnaires are used in clinical trials and include important outcomes such as postoperative pain and related symptoms. For these assessments, in the present study, the following instruments will be used:

a) Functional Assessment of Cancer Therapy - Cervix Cancer (FACT-Cx), version 4.0, in Portuguese (Annex 1).

b) Universal Pain Assessment Tools: comprises the Visual Analog Pain Scale (VAS), the Numeric Visual Pain Scale (EVN) and the Faces Pain Scale (EF) (Annex 2).

4.11. Study interruption rules:

Below are the study interruption criteria:

a) Registration of a single grade 5 adverse event at any stage of the study;

b) Record of two grade 3 or 4 adverse events in the first stage of the study;

c) Record of two grade 3 or 4 adverse events in the second stage of the study;

d) the benefit of using the device under interim analysis;

e) Identification of considerable risk to participants not provided in this research protocol.

In any of the aforementioned situations, the researcher, before interrupting the study, will communicate the Research Ethics Committee (CEP) of the Barretos Cancer Hospital and await the substantiated opinion, unless the risk to the participants is imminent. In the latter situation, the researcher will interrupt the study to safeguard the research participants and will communicate the CEP as soon as possible.

4.12. Study visits and data collection:

TABLE 1 summarizes the activities carried out in the study according to the time of the visits.

4.12.1. Baseline visit:

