At the time of the initial visit, preoperative tests (blood count, serum biochemistry, coagulogram, chest X-ray, electrocardiogram and pregnancy test) and pre-anesthetic evaluation of women in whom CAF is indicated will be checked. This preoperative assessment is done on a routine basis and does not include specific aspects of the study. Women who are eligible for CAF and meet the study's eligibility criteria will be invited to participate in the survey. Those who agree will sign the Informed Consent Form at the initial visit.

During this visit, demographic and clinical information will be collected through interviews and consultation of medical records (Annexes 3). At this time, the quality of life questionnaires will also be applied.

4.12.2. Operative and postoperative visits:

On the day of surgery, a form will be filled out with the data pertinent to the surgical procedure. (Annex 4).

Postoperative visits will take place 15 days (1-PO) and 30 days (2-PO) after surgery. (Annexes 5 and 6). The acceptable windows of opportunity for visits will be ± 3 days. During these visits, the participants will undergo a medical consultation, when anamnesis and gynecological physical examination will be carried out. They will also answer the quality of life questionnaires. Any adverse event will be recorded on a specific form each post-operative visit in accordance with the Common Terminology Criteria for Adverse Events v3.0 (CTCAE V3). (Annex 7).

Participants who have the DUDA device will have it removed during the 2-PO visit during the gynecological examination.

4.12.3. Follow-up visits:

Follow-up visits will take place 3, 6, 12 and 18 months after surgery (respectively FUP-1, FUP-2, FUP-3 and FUP-4) according to our flow chart described below. The acceptable windows of opportunity for visits will be ± 10 days. During these visits, participants will undergo a medical consultation, when anamnesis and gynecological physical examination will be performed, which will include the collection of material for cervical cytology, hysterometry to assess the permeability of the endocervical canal and colposcopy to visualize the squamocolumnar junction. The degree of permeability of the channel will be recorded in a specific form. During follow-up visits, quality of life questionnaires will also be applied and adverse events will be recorded and follow-up information will be collected (Annex 8-11).

4.12.4. Surgery information:

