8. ETHICAL ASPECTS

8.1. Special thematic area:

The present study fits into the special thematic areas “therapeutic equipment and devices, new or not registered in the country” and “new invasive therapeutic procedures”, which are provided for in CNS Resolution 466/12, respectively in items IX.4.3 and IX .4.4. After analysis and approval by the Research Ethics Committee of the Barretos Cancer Hospital, the protocol will be forwarded to the National Research Ethics Commission (CONEP).

This research does not involve other special thematic areas.

8.2. Consent Form:

Applicants eligible for the study will be invited to participate in the research, giving them the necessary explanations and the time necessary to clarify doubts for autonomous decision making. There will be two consent forms, one for the first stage of the study (without randomization) and another for the second stage (with randomization).

8.3. The weighting of risks and benefits:

Women who participate in the study and who use the DUDA device may, in theory, have reduced the chance of endocervical canal stenosis after CAF. However, there is still no certainty about this benefit. As in any other clinical trial that evaluates new devices, there is the possibility of the occurrence of adverse events, such as genital bleeding and uterine infection, and others that are not predicted. A previously published uncontrolled clinical trial with 33 women who used an endocervical device after conization did not report any complications related to bleeding or infection. Based on this essay, it is believed that research participants will not be exposed to excessive risks.

8.4. Biological material bank:

This study will not constitute a biobank or biorepository.

8.5. Infrastructure and human resources:

The Barretos Cancer Hospital has the appropriate infrastructure to perform the surgical procedures and to provide the necessary assistance to the participant in case of damages resulting from the research. The responsible researcher and the other researchers have experience in research in the field of oncological gynecology.

8.6. Data confidentiality:

The collection forms, as well as the database, will not contain information that can identify the research participant, preserving their privacy. Participants will be identified by codes and the master list with their identification will be held by the responsible researcher in a safe place.

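### Unblinding is justified only for implanting the device, yet nothing masks the examiner who grades late stenosis at 3 to 18 months, although most of that assessor bias could be removed

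*Protocol*

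**What the plan says.** Protocol section 4.1 describes the design as open and gives a single reason for not blinding: "the doctor must know the result of the randomization for implantation of the device, he will not be blind".

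The primary objective in section 3.1 concerns late stenosis: "To evaluate the effectiveness of a new cervical device called DUDA in preventing late cervical canal stenosis in women undergoing conization".

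Section 4.10.2 assigns the measurement to an unspecified doctor: "the doctor will check the permeability of the canal by introducing the hysterometer through the cervical canal". The result is a three-level grade: "The difficulty of introducing the 2.5mm hysterometer through the channel will be noted according to the following scale". The levels are passage without difficulty, a middle level ("Little / Moderate difficulty, however possible passage of the hysterometer") and failure to pass. None is named as stenosis. The same section also uses the woman's own account of menstrual flow and dysmenorrhea.

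On timing, section 4.12.2 states: "Participants who have the DUDA device will have it removed during the 2-PO visit during the gynecological examination". That visit is at 30 days. Section 4.12.3 and the activity table in 4.12.4 schedule hysterometry at 3, 6, 12 and 18 months only.

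Section 4.5 says that the responsible researcher designed the device. No section says who examines at follow-up, separates that doctor from the surgeon, or explains why the examiner could not be masked.

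**The concern.** The surgeon cannot be blind to whether a device is being sutured in. The doctor who passes a hysterometer months after removal is in a different position, and the protocol lets the surgeon's reason stand for both.

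This matters because the grade is not a pure instrument reading. The line between no difficulty and some difficulty is a judgement. The line between difficult passage and failure is more concrete, but it still depends on how long and how firmly the examiner tries, and the protocol sets no number of attempts or stopping point. An examiner who knows the arm and expects benefit can persist longer in device women or grade them more leniently. The error then goes one way, towards the device. A larger sample would not remove it, and no analysis could repair it. Who examines, and what that person knows, is a matter of trial conduct and belongs in the protocol.

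**Working it through.** **1. Does the stated reason cover the measurement?**

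| Event | Time | Must the doctor know the arm? |
|---|---|---|
| Implantation (4.7) | Day 0 | Yes |
| Postoperative visit (4.12.2) | Day 15 | Device in place and visible |
| Removal (4.12.2) | Day 30 | Yes |
| Hysterometry (4.12.3, activity table) | 3, 6, 12, 18 months | No reason given |

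Every scheduled hysterometry comes after the stated reason has lapsed. Section 6 starts the group comparisons at the 30-day visit, where masking is impossible, but no hysterometry is scheduled then and the objective is late stenosis.

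**2. The plan's own figure.** Section 5.2 gives 104 to 203 per group for 20% or 15% against 6%, alpha 5%, power 80%. With two-sided alpha and pooled variance,

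n = [1.960·√(2p̄(1−p̄)) + 0.842·√(p₁(1−p₁)+p₂(1−p₂))]² / d²

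and with continuity correction n′ = (n/4)·[1+√(1+4/(n·d))]².

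- 20% vs 6%: n = 89.4, n′ = 103.2, rounded up to 104.
- 15% vs 6%: n = 180.9, n′ = 202.6, rounded up to 203.

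Both figures reproduce, but only with continuity correction; without it they are 90 and 181. The point made here disputes neither figure. It does show that the choice of test matters below, because section 6 allows chi-square or Fisher without saying whether the chi-square is corrected.

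**3. Illustration of size.**

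Inputs from the protocol: 120 per arm; true stenosis p = 15% or 20% (the control rates in 5.2); 5% significance level (section 6).

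Assumptions not in the protocol: no true device effect; stenosis means failure to pass; a share m of device-arm failures is recorded as passable, and none in the control arm.

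The recorded device-arm rate is p(1−m). For m = 10%, 25%, 33% this is 13.5%, 11.25%, 10.05% when p = 15%, and 18%, 15%, 13.4% when p = 20%. The expected number of women regraded is 120·p·m: 1.8 to 2.4, 4.5 to 6.0, and 5.9 to 7.9.

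The chance of a significant result is the exact sum of Bin(x; 120, p)·Bin(y; 120, p(1−m)) over all tables (x, y) that the two-sided 5% test rejects.

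| Share m | Uncorrected, p = 15% | Uncorrected, p = 20% | Corrected, p = 15% | Corrected, p = 20% |
|---|---|---|---|---|
| 0 | 5% | 5% | 3% | 3% |
| 10% | 6% | 7% | 4% | 5% |
| 25% | 14% | 18% | 10% | 13% |
| 33% | 21% | 28% | 16% | 22% |

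Almost all of the rejections favour the device. At m = 25% and p = 15%, uncorrected, it is 13.5 of 13.7 percentage points.

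**The case against.** The protocol declares an open design openly and does not contradict itself here. It never says that the follow-up examiner is unblinded. That is inferred from the open label, from the unspecified doctor in 4.10.2 and from the absence of any masking provision. This is fair, but the gap remains: a reason valid for one role is left to cover another.

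The scale is only partly subjective. Whether a fixed 2.5 mm instrument passes is fairly concrete. This also stands, and it limits how much misgrading is plausible if stenosis means failure to pass. If the middle level also counts as stenosis, moving a woman from the bottom level to the middle changes nothing. Any bias would then act at the more judgemental upper boundary, which the illustration does not model.

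Nothing in the protocol supports any particular misgrading share. At one in ten the inflation is small, and with the corrected test the chance of a significant result stays at or below 5%.

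Three stronger readings are tempting, and the document supports none of them.

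- A reader might infer that the device's designer will grade the outcome. Section 4.5 says who designed the device; no section says who examines.
- A reader might infer that the follow-up forms show the arm. The annexes are not available to check.
- A reader might infer that masking would remove the bias entirely. The woman knows her arm and may disclose it, suture marks may remain, and her reported symptoms stay unmasked in any case.

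**Conclusion.** The point holds in this form: section 4.1 justifies unblinding for implantation only, no section masks the late hysterometry, and the primary outcome is therefore exposed to assessor bias that could be largely reduced. It should be changed before the second stage starts.

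The figures show sensitivity and do not predict the trial's error rate. Regrading an expected 4.5 to 6 device-arm women (one in four failures) would take the chance of a significant result under no effect to 14-18% uncorrected or 10-13% corrected. These values rest on failure to pass as the definition of stenosis, true rates of 15-20%, 120 per arm, and misgrading in the device arm alone. It would be wrong to conclude that the planned trial has a false-positive rate of that order, because the actual share misgraded is unknown and could be near zero.

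**What to change.** State in sections 4.1, 4.10.2 and 4.12.3 that at FUP-1 to FUP-4:

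- hysterometry is done and its grade recorded by a doctor of the existing team who did not operate on that woman and did not see or remove the device at the 15- or 30-day visit;
- it is done before the history is taken and before the surgical record is opened;
- the woman is asked beforehand not to disclose her arm;
- the grade is entered on a form that does not show the arm.

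Section 4.1 should then limit its reason for unblinding to implantation, the day-15 visit and removal.

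The sample size, visits and tests do not change. The cost is rostering, plus a fixed order within the visit. Two departments take part (4.2), and section 8.5 refers to several researchers: "The responsible researcher and the other researchers have experience in research in the field of oncological gynecology". That makes the arrangement plausible, but the protocol does not say how many doctors do follow-up, so the sponsor should confirm that enough remain after the exclusions.
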